**SENSITIVITY**			
Patient-reported Health-Related Quality of Life (HRQOL) outcome	Improved	HRQOL scores, measured by the EQ-5D-5L at 12 weeks	Independent t-test/ linear regression with multiple imputation for missing data

*Expected that RTS-Lobectomy will improve or be more, less, fewer or shorter than VATS-Lobectomy for each variable/outcome.

#### Primary analysis

The HRQOL of the patients will be described using both the EQ-5D-5L descriptive system as well as the corresponding utility scores calculated using the Canadian EQ-5D-5L value set [19]. The effect size using the EQ-5D-5L utility scores will be used to compare the difference in HRQOL between the two treatment arms.

### Secondary analysis

Short-term clinical outcomes will involve aspects of perioperative care:
○ A higher quality of pathological staging is expected to occur with participants who have RTS-Lobectomy. Data on clinical and pathological staging will be compared.○ More lymph nodes are expected to be sampled for participants who have RTS-Lobectomy. The number of lymph nodes sampled for each patient will define the outcome measure.○ A shorter duration of chest tube drainage is expected to occur for participants who have RTS-Lobectomy. This will be measured by the number of days between the date of surgery and the date of chest tube removal.○ A shorter hospital length of stay is expected to occur for participants who have RTS-Lobectomy. This will be measured by the number of days between the date of hospital admission and the date of discharge.○ Less intraoperative blood loss (mL) is expected to occur for participants who have RTS-Lobectomy. This will be measured by the volume of blood loss in mL intraoperatively for each patient.○ Less post-operative analgesia requirements are expected to occur with participants who have RTS-Lobectomy. This will be measured by collecting the amount of analgesia consumed by each participant (e.g., type of medication used (e.g., PCA, epidural, intravenous, oral), the number of days the medication was used, and the amount used) in hospital.○ Less post-surgical pain is expected to occur in participants who have RTS-Lobectomy. This will be measured by collecting the pain score for each participant daily during their hospital admission.Resource Utilization and Cost Effectiveness
○ The cost analysis will only involve aspects of intraoperative and postoperative care because the preoperative evaluation of patients in both groups is identical. For robotic costs, calculating depreciation and maintenance costs for robotic equipment, based on the percent utilization of robotic resources by the thoracic surgery service will be done. Total costs will be calculated using the natural units of the relevant health care resource used by each participant and the unit costs for each resource item. QALY will be calculated by the area under the curve method, using health utility measured by EQ-5D-5L and the corresponding time duration. The incremental cost per QALY gained is calculated using the difference in the total cost divided by the difference in mean QALYs between RTS- and VATS-Lobectomy. Sampling uncertainty will be handled using the nonparametric bootstrapping approach. Cost effectiveness curves will be used to calculate the probability of RTS-Lobectomy being more cost effective than VATS-Lobectomy in treating this patient population at a wide range of maximum willingness to pay thresholds.HRQOL
○ The HRQOL will be analyzed as per the primary outcome at weeks 3 and 7, and months 6 and 18, and 1-, 2-, 3-, 4- and 5-years.Survival Analysis
○ Time to event analysis models will be used to compare overall survival at 3 years and 5 years between trial arms.

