**Methods:**

The RAVAL trial will be conducted in two phases: Phase A will enroll 186 early-stage non-small cell lung cancer patients who are candidates for minimally invasive pulmonary lobectomy; while Phase B will continue to recruit until 592 patients are enrolled. After consent, participants will be randomized in a 1:1 ratio to either robotic- or video-assisted lobectomy, and blinded to the type of surgery they are allocated to. Health-related quality of life questionnaires will be administered at baseline, postoperative day 1, weeks 3, 7, 12, months 6, 12, 18, 24, and years 3, 4, 5. The primary objective of the RAVAL trial is to determine the difference in patient-reported health-related quality of life outcomes between the robotic- and video-assisted lobectomy groups at 12 weeks. Secondary objectives include determining the differences in cost-effectiveness, and in the 5-year survival data between the two arms. The results of the primary objective will be reported once Phase A has completed accrual and the 12-month follow-ups are completed. The results of the secondary objectives will be reported once Phase B has completed accrual and the 5-year follow-ups are completed.

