#### Enrollment and baseline

Potential participants will be screened to determine if they meet the eligibility criteria. Potential participants who meet the eligibility criteria will be approached by a trial coordinator to determine if they agree to participate. If they agree, they will be asked to and sign the PICF. Once the PICF is signed, they will be considered enrolled, and the participant will be randomized, asked to complete the Trial Health Questionnaire and be provided a Study Diary.

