#### Follow-up assessment

Follow-up will occur at weeks 3, 7, and 12; then months 6, 12, 18, and 24; and then years 3, 4, and 5 from the date of hospital discharge. All follow-up assessments, except for the 7-week, will take place in the hospital clinic at the time of the participant’s routine follow-up visits with the surgeon. The trial coordinator will be available to assist the participant in completion of the Trial Health Questionnaire as well as review the Study Diary with the participant. At the 7-week trial follow-up assessment, the trial coordinator will collect the data over the telephone. Five-year survival data will also be obtained by conducting a quick chart review at five-years. The patients have routine surveillance follow-up appointments with the surgeon every 6 or 12 months after surgery, either in-person or virtually, so survival data will be available from the surgeon’s surveillance follow-up note at five years.

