## Statistical methods

### Statistical methods for primary and secondary outcomes

Baseline characteristics of both treatment groups will be compared to ensure homogeneity in the patient population. Descriptive statistics will be reported by treatment group where categorical variables will be reported as counts (percentages) and continuous variables as mean (standard deviation) or as median (25^th^ percentile, 75th percentile). All analyses of primary and secondary outcomes will be carried out based on the intention-to-treat principle. Unadjusted comparisons of continuous outcome measures will be carried out using an independent t-test or the Wilcoxon rank-sum test if the assumptions of the t-test were violated. Unadjusted comparisons of categorical outcome measures will be computed using the chi-squared test, or the Fisher’s exact test if any of the expected values in the contingency table is less than 5, or McNemar’s test. For adjusted analyses, multivariable logistic regression analyses will be used for binary outcomes and multivariable linear regression for continuous outcomes. The results of comparisons between groups will be presented as mean differences for continuous outcomes and relative risks or odds ratios for binary outcomes, with corresponding 95% confidence intervals and associated p-values. ANOVA will be used for repeated measures. Survival will be compared using the Kaplan-Meier method and cox proportional hazard models. Survival curves will be compared using the Log-rank test. P-values will be reported to three decimal places with p-values less than 0.001 reported as p < 0.001. All analyses will be performed using SAS. Table 3 provides a summary of the variables, measures and methods of analysis.

**Table 3 pone.0261767.t003:** Variables, measures and methods of analysis.

Variable/Outcome	Hypothesis*	Outcome	Method of Analysis

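### The cost-effectiveness rule divides by a difference in mean QALYs with no adjustment for baseline EQ-5D-5L utility, which costs precision and lets chance imbalance into the ICER

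*Protocol article*

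**What the plan says.** The rule is in the Secondary analysis section, under resource utilisation and cost effectiveness. QALYs are defined this way: "QALY will be calculated by the area under the curve method, using health utility measured by EQ-5D-5L and the corresponding time duration". The ICER is then "calculated using the difference in the total cost divided by the difference in mean QALYs between RTS- and VATS-Lobectomy". On uncertainty: "Sampling uncertainty will be handled using the nonparametric bootstrapping approach". Acceptability curves follow from that.

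No covariate is named for the QALY difference. The cost-effectiveness row of Table 3 gives only the incremental cost per QALY, while the rows for lymph nodes, blood loss and analgesia each list linear regression. The general Statistical methods text offers "multivariable linear regression for continuous outcomes" for adjusted analyses, but names no covariates and does not mention QALYs.

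The baseline value is available. The abstract states: "Health-related quality of life questionnaires will be administered at baseline, postoperative day 1, weeks 3, 7, 12". Under Enrollment and baseline, once consent is signed, "the participant will be randomized, asked to complete the Trial Health Questionnaire and be provided a Study Diary".

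**The concern.** Area under a utility curve is a level, not a change. Patients who start with higher utility tend to have higher utility at later visits, and so a larger area. If one arm happens to start higher, part of that head start appears as QALYs gained by that arm.

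The incremental cost per QALY is a secondary outcome computed in both phases. A difference between two minimally invasive lobectomies may be modest on the QALY scale, so an avoidable component of noise in the denominator matters. The Sample size section itself says that QALY differences are harder to detect than the primary outcome. Leaving a pre-operative measure of the same quantity unused works against that.

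**Working it through.** **Inputs from the article.** Utility SD 0.16 and MID 0.07; 83 evaluable and 93 recruited per arm in Phase A; 296 per arm in Phase B (Sample size). Visits are timed from hospital discharge (Follow-up assessment). Median stay is 4 days (Introduction).

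**Assumptions not in the article.** The SD of 0.16 applies at every visit; the correlation rho is equal between all visits and lies between 0.3 and 0.7; there is no gap between baseline and surgery; data are complete.

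**Reproducing the plan's figure.** n per arm = 2 × (1.96 + 0.842)² × (0.16/0.07)² = 82.01, rounded up to 83, or 166 in total. 83/0.9 = 92.2, rounded up to 93 per arm, or 186. The plan's numbers reproduce, so SD 0.16 is its working value.

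**Size of a chance baseline difference.** SE = 0.16 × √(2/n).
- 93 per arm: 0.0235, 95% range ±0.046.
- 296 per arm: 0.0132, 95% range ±0.026.

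**Carry-over into one-year QALYs.** Measurements fall at baseline (day 0) and at days 1, 25, 53, 88, 186 and 369 from surgery. In years, the trapezoid weights sum to W = 1.011, the baseline point has weight w0 = 0.0014, and the squared weights sum to S = 0.258. Then:
- slope of the QALY difference on the baseline difference: b = rho × W + (1 − rho) × w0
- variance factor of the unadjusted difference: v = rho × W² + (1 − rho) × S
- SE unadjusted = 0.16 × √(2/n) × √v; SE adjusted = 0.16 × √(2/n) × √(v − b²); share of variance removed = b²/v

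Example at rho 0.5: b = 0.506, v = 0.640, b²/v = 0.256/0.640 = 40%.

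| rho | b | 95% carry-over, 93/arm | 95% carry-over, 296/arm | SE unadjusted → adjusted, 93/arm | variance removed |
|---|---|---|---|---|---|
| 0.3 | 0.304 | ±0.014 | ±0.008 | 0.0164 → 0.0147 | 19% |
| 0.5 | 0.506 | ±0.023 | ±0.013 | 0.0188 → 0.0145 | 40% |
| 0.7 | 0.708 | ±0.033 | ±0.018 | 0.0209 → 0.0127 | 63% |

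Simulation of 4,000 trials on the same schedule gave matching results: 0.0162 → 0.0146, 0.0185 → 0.0145 and 0.0211 → 0.0127. The mean difference was about 0 with and without adjustment in a separate simulation of 4,000 trials that placed baseline four weeks before surgery.

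**Scale.** A full 0.07 gain held to day 88 and gone by day 186 is worth (0.07 × 88 + 0.07 × 98/2)/365 = 9.59/365 = 0.026 QALY. At rho 0.5, matching the adjusted precision without adjustment would take 1/(1 − 0.40) = 1.67 times as many patients.

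**Source of the effect.** The baseline point has almost no weight in this calculation, so the carry-over comes from correlation between baseline and follow-up. In the simulation with baseline four weeks before surgery, the unadjusted SE at rho 0.5 was 0.0195; dropping the pre-operative segment lowered it only to 0.0183, whereas adjustment lowered it to 0.0148. Moving the start of the curve does not solve the problem.

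**The case against.** The strongest reply is that nothing here is biased. Randomisation balances baseline utility in expectation, chance imbalance is ordinary sampling variance, and the bootstrap reflects it. That stands. What remains is that the bootstrap stays centred on the imbalanced estimate and that the variance is avoidable.

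A second reply is that covariates are commonly left to a statistical or health-economic plan, that the article never uses the word unadjusted, and that a regression-adjusted contrast is still a difference in means. This has some force. But the section states the estimator rather than deferring it, and a literal reading gives two arm means subtracted. The general regression sentence does not alter that for QALYs.

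A third reply is that the sizes depend on an assumed correlation structure, and that equal correlation between a pre-operative value, postoperative day 1 and month 12 is a simplification. That is correct, which is why a range is given.

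A reader might go further and infer that the utility curves start at the enrolment questionnaire, so that pre-operative waiting time is credited as QALYs gained. The documents do not support this. The section gives no start point, and a baseline questionnaire does not imply one. The level of utility over a wait common to both arms cancels, and no differential wait is documented. Linear interpolation back from the first post-operative value would leave a residue of d × (W − 1)/2 utility-days for a first difference d and a wait of W days. With d = 0.07 and assumed waits of 14 to 56 days, that is 0.001 to 0.005 QALY, and the article states no wait.

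Nor is the cost window a flaw in itself. The statement "The cost analysis will only involve aspects of intraoperative and postoperative care" comes with a reason: the preoperative work-up is the same in both groups.

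**Conclusion.** The point holds as one of efficiency and of protection against realised imbalance, not of systematic bias. The ICER denominator as written ignores a prognostic measure that the trial already collects. At 93 per arm the 95% range of the carry-over is about ±0.014 to ±0.033 QALY over one year, which spans the 0.026 QALY worth of a full MID gain that fades by month 6. At 296 per arm it is ±0.008 to ±0.018. With 83 evaluable per arm it would be slightly wider, ±0.015 to ±0.034. These figures rest on SD 0.16 at every visit and on equal correlation of 0.3 to 0.7. The article gives no expected QALY or cost difference, so it cannot be said that the ICER would change sign.

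The time origin is a clarification only. The article does not state it, while costs begin at the operation and later visits are counted to "years 3, 4, and 5 from the date of hospital discharge".

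**What to change.** In the cost-effectiveness paragraph of Secondary analysis, define the QALY difference as the arm coefficient from a linear regression of each patient's QALY on arm, baseline EQ-5D-5L utility and surgeon (the randomisation stratum). Refit it in every bootstrap resample together with the cost difference, resampling whole patients so that cost and QALY stay paired. Report the unadjusted ICER beside it.

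For clarity, add that costs and QALYs share one origin, the date of surgery, and run to a fixed horizon from that date in each phase.

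The cost is two sentences and one regression step in the bootstrap. Baseline utility, surgeon and date of surgery are already recorded. The headline ICER becomes an adjusted figure, which the unadjusted one alongside makes transparent.

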### Interim analyses

There are no planned interim analyses.

### Methods for additional analyses (e.g., subgroup analyses)

Subgroup analyses are planned to determine the impact of each of the following subgroups on the effectiveness of RTS-Lobectomy: body mass index (BMI), tumour size, and institution. Our hypothesis is that patient-reported health-related quality of life outcomes will be improved in the RTS-Lobectomy group than the VATS-Lobectomy group for patients who have a higher BMI, a larger tumour size, and had their minimally invasive lobectomy at a high-volume institution because data has shown that the rate of conversion to a thoracotomy is lower in RTS-Lobectomy versus a VATS-Lobectomy for these subgroups [20–23]. Regression using two-way interactions between the two study arms (RTS-Lobectomy versus VATS-Lobectomy) and each subgroup variable will be conducted to examine subgroup effects.

### Methods in analysis to handle protocol non-adherence and any statistical methods to handle missing data

Intention-to-treat implies all participants randomized are included in the analysis based on the treatment they were randomized to. We will impute missing data using multiple imputation [24] for the primary outcome only.

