### Sample size

#### Primary outcome in Phase A

The sample size for the primary outcome in Phase A was calculated based on the Minimally Important Difference (MID) of the EQ-5D-5L derived utility scores among lung cancer patients in the United States of America (USA). The index-based score is typically interpreted along a continuum where 1 represents full health and 0 represents dead, with some health states being worse than dead (<0). A MID of 0.07 and SD of 0.16 is considered clinically significant for this patient population [13]. The MID of 0.07 was considered clinically significant for this patient population because in 2007, Pickard et al. had reported that for EQ-5D utility scores in the USA, MIDs, grouped by performance status, ranged from 0.07 to 0.09 for all cancers and for lung cancer, but when based on FACT-G quintiles, MIDs were 0.06 to 0.07 in all cancers, and 0.05 to 0.06 in lung cancer [13]. A sample size of 166 patients, with 83 patients per arm will ensure detection of this difference with 80% power at a level of significance of 0.05. A 10% drop out rate was used to account for those potential withdrawals, therefore a total of 186 participants will be recruited to the trial, 93 participants per trial arm.

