**SECONDARY**			
Short-Term Clinical Outcomes			
*Pathological Staging*	Improved	Pathological stage	McNemar’s test
*Lymph nodes*	More	Number of lymph nodes harvested	Independent t-test, Wilcoxon rank sum test/linear regression
*Duration of chest tube drainage*	Shorter	Number of days between surgery and chest tube removal	Kaplan-Meier method, Cox regression
*Hospital length of stay*	Shorter	Number of days between admission and discharge	Kaplan-Meier method, Cox regression
*Intra-operative blood loss*	Less	Volume of Intra-operative blood loss (mL)	Independent t-test/Wilcoxon rank sum test/ linear regression
*Post-operative analgesia requirements*	Less	In-hospital consumption (days, type, amount)	Independent t-test/Wilcoxon rank sum test/linear regression
*Chronic post-surgical pain*	Less	In-hospital pain (daily, scale)	Independent t-test/Wilcoxon rank sum test/ANOVA
Patient-reported Health-Related Quality of Life (HRQOL) outcomes	Improved	HRQOL scores, measured by the EQ-5D-5L at 3 and 7 weeks, and 6 and 18 months, and 1,2, 3, 4 and 5 years	Examine the distributions/ regression/ANOVA
Resource Utilization and Cost Effectiveness	More	Resource utilization tracking system, EQ-5D-5L, Return to Normal Living Index (RNLI), and employment status at 12 months	Incremental cost per quality-adjusted life year (QALY) gained will be calculated
Overall Survival	Improved	5-year survival difference	Kaplan-Meier method and cox proportional hazard models. Survival curves will be compared using the Log-rank test

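### Multiple imputation for the primary outcome only, together with repeated-measures ANOVA, leaves secondary HRQOL and QALY analyses with no stated way to keep patients who miss visits, contrary to the all-randomized intention-to-treat promise

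*Protocol article*

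**What the plan says.** Four statements in the protocol article bear on this point.

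- **Missing data.** The section on non-adherence and missing data says: "We will impute missing data using multiple imputation [24] for the primary outcome only". Table 3 lists that imputation in its sensitivity block, for the 12-week EQ-5D-5L.
- **Analysis set.** *Statistical methods for primary and secondary outcomes* says: "All analyses of primary and secondary outcomes will be carried out based on the intention-to-treat principle". The missing-data section defines the term: "Intention-to-treat implies all participants randomized are included in the analysis based on the treatment they were randomized to".
- **Longitudinal HRQOL.** The same statistical methods section says: "ANOVA will be used for repeated measures". Table 3 gives the method for secondary HRQOL as "Examine the distributions/ regression/ANOVA". *Secondary analysis* adds: "The HRQOL will be analyzed as per the primary outcome at weeks 3 and 7", and continues with the later visits up to year 5.
- **QALYs.** *Secondary analysis* says: "QALY will be calculated by the area under the curve method, using health utility measured by EQ-5D-5L and the corresponding time duration". The Phase A sample size section describes the utility scale as one where "1 represents full health and 0 represents dead".

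The Phase B sample size section gives QALY differences, along with five-year survival, as a reason for repowering the trial to 592.

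**The concern.** The word *only* makes the imputation rule a fixed choice. It excludes imputation for every other EQ-5D-5L visit, for QALYs and for costs, so an analysis plan that imputed them would contradict the article. No likelihood-based method is named that would use incomplete records without imputation. Secondary HRQOL and QALYs therefore fall back on complete or available cases, while the same document promises that every randomized patient is included.

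The named longitudinal method adds to the problem. Classical repeated-measures ANOVA works on complete records, so one missed questionnaire in five years removes the patient. Death removes the patient too, and the trial hypothesises that mortality differs between arms. A QALY is a sum over the whole horizon, so one gap leaves it incomplete.

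At stake are precision and comparability between arms for the longer-term HRQOL results and the incremental cost per QALY. The 12-week primary comparison is not affected.

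**Working it through.** **1. The plan's own figure.** The Phase B section gives a 10-point difference in five-year survival, the Freedman log-rank method, 80% power, alpha 0.05 and N = 592, but not the two survival rates. Trying 70% versus 80%:

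- HR = ln 0.80 / ln 0.70 = 0.626
- events = (1.96 + 0.842)² × [(1 + HR)/(1 − HR)]² = 7.85 × 18.85, which rounds up to 148
- N = 148 / (1 − 0.75) = 592

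This matches exactly. Neighbouring pairs come close (69%/79% gives 608, 71%/81% gives 580) and more distant ones do not (60%/70% gives 712, 75%/85% gives 510). The rates 70% and 80% are therefore inferred, not stated.

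**2. Loss through death alone.** Alive at five years: 296 × 0.70 ≈ 207 and 296 × 0.80 ≈ 237, together 444 of 592 (75%). A listwise ANOVA through year 5 loses the other 25% even if no survivor misses a form.

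**3. Loss through missed questionnaires.** The abstract lists 12 assessments: baseline, day 1 and ten follow-ups. The article gives no per-visit missingness m, so m is an assumption, taken as independent between visits. Complete fraction = 0.75 × (1 − m)^12.

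| m per visit | complete | of 592 |
|---|---|---|
| 1% | 67% | 394 |
| 3% | 52% | 308 |
| 5% | 41% | 240 |
| 10% | 21% | 125 |

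Counting only the ten follow-ups gives 68% at 1% and 45% at 5%. The complete fraction falls below one half only when m exceeds 1 − (0.5/0.75)^(1/12) = 3.3% for 12 assessments, or 4.0% for ten.

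The only dropout figure in the article is the 10% used for Phase A. Applied as a single permanent dropout, it leaves 0.75 × 0.90 = 67.5%, about 400 patients.

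**4. Shorter horizon.** Table 3 mentions 12 months in the cost row, and Phase A also has a cost-effectiveness analysis. Up to month 12 there are seven assessments. Ignoring deaths, (1 − m)^7 gives 87% complete at m = 2% and 70% at m = 5%.

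**5. What the rule for death governs.** With exponential survival, no discounting and equal utility in both arms, mean life-years over five years are (1 − S)/λ with λ = −ln S / 5. This gives 4.21 at S = 0.70 and 4.48 at S = 0.80, a difference of 0.276. At a constant utility of 0.7 to 0.9 that is 0.19 to 0.25 QALY, which appears only if time after death counts as 0. The article does not say that it is left out. The figure only shows why one sentence on the matter is worth adding.

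**The case against.** The strongest reply is that the article does not commit secondary HRQOL to one listwise ANOVA. Table 3 also lists regression, and *Secondary analysis* can be read as a separate comparison at each visit. Such a comparison uses everyone observed at that visit, up to about 75% at year 5. Loss to follow-up is expected to be minimal, with telephone and late-visit recovery. Independent missingness also understates the complete fraction if missed visits cluster in the same patients. All of this stands, and it limits the size of the problem. It does not resolve the conflict with the all-randomized promise, because a visit-by-visit analysis without imputation still leaves out whoever is missing.

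For QALYs, an area under the curve could bridge an isolated gap by joining the neighbouring scores. That is itself an unstated single imputation, and it cannot bridge a gap at the end of follow-up.

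Three stronger readings are tempting, and the document does not support them:

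- **Most of the sample is discarded.** This needs listwise ANOVA over all visits and more than about 3 to 4% independent missingness per visit.
- **QALYs are restricted to survivors.** No sentence says so. The area-under-the-curve method with dead anchored at 0 is compatible with scoring deaths as 0, and the detail may sit in an analysis plan that is not shown.
- **Any survival benefit is lost.** Overall survival is a separate secondary outcome with Kaplan-Meier, log-rank and Cox analyses.

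Adjusting QALYs for baseline utility may likewise be left to the analysis plan, and its absence here is no fault.

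**Conclusion.** The point holds as an inconsistency between stated rules. Imputation is limited to the primary outcome and ANOVA is the named repeated-measures method, so secondary HRQOL and QALYs have no stated method that keeps patients with missing visits. Intention-to-treat on all randomized patients is nevertheless promised for them.

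If longitudinal HRQOL is analysed by classical repeated-measures ANOVA through year 5, the loss is at least the roughly 25% who die. Complete patients then range from about 67% at 1% missing per visit to 41% at 5%. These figures rest on inferred 70%/80% survival, assumed and independent missingness, and 12 assessments. Visit-by-visit regression loses less. The direction of any bias cannot be derived from the document. The change should be made before the Phase B data are analysed.

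**What to change.** 1. **Longitudinal HRQOL.** Replace repeated-measures ANOVA with a likelihood-based mixed model on all available scores, with arm by visit, baseline utility and surgeon (the randomization stratum) as terms.
2. **QALYs and costs.** Reword the missing-data section so that multiple imputation also covers the EQ-5D-5L and cost items feeding QALYs and the incremental cost-effectiveness ratio. State how it is combined with the planned bootstrap, and keep complete-case as a sensitivity analysis.
3. **Death, as a clarification.** Confirm that QALYs take utility 0 from the date of death, in line with the scale anchor, and that scores after death are not imputed. Label late HRQOL results as applying to survivors and read them beside overall survival. The mixed model does not settle this alone, because it treats scores after death as ordinary missing data.

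The cost is analysis wording and modest extra programming. Item 3 also needs dates of death, whereas the follow-up data section limits the five-year survival item to alive or not. The downside is a missing-at-random assumption for questionnaires and costs, which the complete-case analysis helps to probe but cannot test.
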